### Conceptual framework

This project is guided by the diffusion, dissemination and implementation of innovation conceptual framework described by Greenhalgh et al. [34]. This model describes characteristics of successful innovations and diffusion and dissemination methods for implementing new ways of practicing. Innovations are defined as a ‘novel set of behaviours, routines and ways of working that are directed at improving health outcomes, administrative efficiency, cost effectiveness, users’ experience and that are implemented by planned and coordinated actions’ ([34], p. 582). When describing the spread of innovation in service organisations, Greenhalgh et al. differentiated three conceptual and theoretical bases, ‘let it happen’, ‘help it happen’ and ‘make it happen’ and defined their key features ([34], p. 593). Our study will address the ‘help it happen’ concept by negotiating, influencing and enabling the use of evidence-based practice by AHPs that work with children with cerebral palsy.

### Overall purpose and hypotheses

This study aims to *improve allied health professional research implementation behaviours* using a tailored multi-strategy intervention package [33] and to reduce the research-practice gap in multiple organisations that provide services to children with cerebral palsy.

Our specific research questions includeDoes the tailored multi-strategy intervention change AHP behaviours via greater use of evidence-based outcome measures and/or interventions, and improved AHP knowledge of evidence-based interventions and outcome measures for children with cerebral palsy?How does AHP knowledge of evidence-based interventions and outcome measures for children with cerebral palsy in the four organisations in which the intervention is introduced compare to the organisation in which the practices are mandated?What is the relationship between the numbers and/or type of barriers to knowledge translation and the level of uptake of routine use of outcome measures in different healthcare organisations?How do barriers in the four organisations in which the intervention is introduced compare to the organisation in which the practices are mandated?How does the size and scope of the organisation impact the implementation of the multi-strategy approach?Do time trends show a reduction in rates of adverse outcomes, including severe scoliosis, hip dislocation (MP >100%) and progressive limb contractures over the study period, for children with cerebral palsy whose parents consent to be a part of this project? If so, are these trends comparable to Swedish cerebral palsy follow-up outcomes?

## Methods/design

### Research design

This study will employ a before and after design [35] in four Australian non-government organisations that provide allied health services to children with cerebral palsy, with a fifth organisation acting as a comparison site. Included organisations are Yooralla and Kids Plus in Victoria, St Giles in Tasmania, Novita Children’s Services in South Australia and Cerebral Palsy Alliance in New South Wales. Cerebral Palsy Alliance will act as a comparison site as the tailored intervention is mandated in that organisation and embedded in routine practice following a randomised controlled trial [33]. By mandating these practices, the Cerebral Palsy Alliance is deemed to be operating according to the ‘make it happen’ concept ([34], p. 593). Having a comparison site in which the tailored intervention is in routine use affords the opportunity to examine the process of diffusion of innovation and describe features that may account for the success or failure of the tailored intervention in different organisations, as recommended by Greenhalgh et al. ([34], p. 615–6), and articulated in research questions two and three above. Measures of clinician practices at each site will be collected at baseline (prior to implementation of the intervention) and at 6, 12 and 24 months following implementation. The total study duration is 3 years.

### Participants and recruitment

AHPs: All physiotherapists, occupational therapists and speech pathologists working, or having the potential to work with children with cerebral palsy in participating service providers, will be eligible to participate. Organisation-specific recruitment strategies will be implemented including advertising posters, newsletter commentaries, email contact and face to face sessions for staff and families. Written informed consent will be sought from AHPs; consent to participate is voluntary, and there will be no adverse consequences for any eligible participant who chooses not to take part.Children and families: Children aged 3–18 years with a diagnosis of cerebral palsy will also be recruited to the study. All families whose children with cerebral palsy receive services at participating organisations will be provided with detailed information about the study. Consent to collect longitudinal child-specific data to monitor health service inputs and outcomes related to the project will be sought. Again, consent to participate will be voluntary, and there will be no adverse consequences for any eligible participant who chooses not to take part.

### Ethics

Ethical approval for this study has been granted from the Australian Catholic University Research Ethics Committee (Reference: 2013-309 V), the Department of Education and Early Childhood Development (Reference: 2013_001962) and the Cerebral Palsy Alliance Research Ethics Committee (Reference: 2013-04-02). Approval documents from the Australian Catholic University Research Ethics Committee were lodged and accepted by each partner organisation’s ethics committee or chief executive officer.

### Intervention

The tailored multi-strategy intervention aims to address known barriers to evidence use and will consist of:Identification of ‘*Knowledge Brokers*’ (expert research translators) based at each organisation who will aim to redress workplace barriers unique to each site. Each organisation will nominate one or more knowledge brokers for their site who has demonstrated leadership skills, excellent communication skills, peer respect and a specific interest in evidence-based practice. The knowledge brokers will work with the project team, the organisation’s management and the AHPs to act as agents in the process of translating and contextualising evidence for users within the organisation. This will involve taking part in training and cross-organisational knowledge broker support groups to develop the knowledge brokering role, identifying facilitators and ameliorating context-specific barriers, contributing to the delivery of education packages and providing day-to-day support to AHPs as they engage in project activities and outcomes.Provision of a *customised e-evidence library*—‘*CP Decision*’ [36]—to enable AHPs rapid and real-time access to synthesised and critiqued cerebral palsy research evidence. This library employs a traffic light system corresponding to evidence levels [21] and will be updated on an ongoing basis to accommodate new evidence as it emerges. The resource also contains a suite of decision-making intervention algorithms based on best available evidence in addition to research on cerebral palsy prognosis and assessment. The purpose of providing *CP Decision* is to decrease the amount of time it takes AHPs to retrieve the highest levels of published evidence.*Negotiated education and professional development days* for AHPs at partner organisations (implemented by the project investigators and the organisation-based knowledge brokers) about ‘how to’ implement or administer the current and most effective treatment and measurement options for cerebral palsy, using concrete and precise descriptions of the clinical processes involved.Provision of an *electronic cerebral palsy clinical outcomes database* (CP Check-Up™, provided by Cerebral Palsy Alliance). This electronic tool will be used by AHPs to record routine valid and reliable clinical measurements of participating children and to summarise the therapeutic interventions provided to these children. Through instant generation of an electronic report, the tool will provide real-time feedback about changes in outcomes of individual children over time, guiding evidence-based clinical decision-making to support direct therapeutic intervention and timely referral to ancillary services.

### Outcome measures

*Change in AHP behaviour* (use of evidence-based outcomes and interventions, research question 1) will be determined in two ways:(i).The Best Service Best Time Evaluation questionnaire of evidence-based practice behaviours reported by participating AHPs (adapted from Campbell et al. [33] and Aarons [37]) will be collected on four occasions: baseline, 6, 12 and 24 months. In addition to participant demographics, the questionnaire describes evidence-based practice behaviours such as client goal setting, use of research and use of measures to inform clinical decision-making.(ii).Data extracted from the electronic cerebral palsy clinical outcomes database. This tool and associated database has been developed for the Australian context by Cerebral Palsy Alliance, the study comparison site, and is based on the Swedish cerebral palsy follow-up surveillance programme [14-16]. It is used to collate data from a range of evidence-based outcome measures and to record interventions provided. A minimum dataset within the clinical outcomes database has been defined for this project and includes elements related to the general description of cerebral palsy type, distribution, associated impairments, mobility and lower limb functions, upper limb and self-care functions, communication and swallowing abilities and nutrition.

Children aged less than 6 years will be assessed at 6 monthly intervals; children aged 6–18 years will be assessed at baseline, 6, 12 and 24 months. Data extracted from the clinical outcomes database to determine change in AHP behaviour will include proportion of eligible professionals routinely contributing data, proportion of clinical outcome measures completed per child, proportion of cerebral palsy caseload with data reported and comparisons between expected proportions in the population who might be eligible for specific management, such as hip surveillance, and the observed proportions receiving them.

*Change in AHP evidence-based practice knowledge* (research question 1) will be measured using the Evidence Based Practice and Outcome Measurement Competency quiz [33] that has been integrated into the Best Service Best Time Evaluation for the purposes of this study. This knowledge quiz includes open-ended questions developed by a panel of experts and assesses AHP’s knowledge of reliable, valid measures used in cerebral palsy and the current level of evidence for interventions used for children with cerebral palsy. This measure will be implemented at baseline, 6, 12 and 24 months.

*Impact of organisational factors on implementing the strategies* (research questions 2 and 3) will be assessed using mixed methods, including a questionnaire that evaluates AHP perception of the extent to which organisational factors act as supports or barriers to implementation of evidence-based practices (Supports and Barriers Questionnaire, adapted with permission from [38]) and qualitatively through focus groups and interviews. Focus groups will include three groups of participants, each with representatives from the participating organisations: (1) knowledge brokers, (2) clinical services managers and (3) participating AHPs. Interviews will be conducted with senior managers or chief executive officers.

*Longitudinal outcomes of children with cerebral palsy* (research question 4) will be assessed using clinical data extracted from the clinical outcomes database. Specific musculoskeletal measurements will be modelled from data collected at 6, 12 and 24 months.

Additional data relating to potential confounders for uptake of evidence-based practices will be collected including organisational characteristics such as profile of children attending the service (multiple diagnoses or only cerebral palsy), size and number of sites that an organisation operates from and professional characteristics of AHPs including discipline, years of experience and proportion with higher degrees. In addition, a record of implementation at each site, including number and timing of recruitment of knowledge brokers and staff, days and topics of professional development provided and frequency of hits (number of times accessed) on the e-library, will be kept to provide process measures for the study.

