### Estimated sample size and power of the study

Based on organisational commitment to the project, and expected workforce changes during the course of the study, it is anticipated that 80% of the eligible AHPs will take part in the study (i.e. 192 participants from an estimated 240 eligible AHP participants across all partner organisations). Calculations indicate that this sample will be sufficient to detect a difference of 6 points on the Best Service Best Time Evaluation with >90% power.

Pre-study estimation of the number of participating children suggests a sample size of 614 may be achieved (80% of the 768 eligible children identified across all partner organisations).

A 10% arithmetic difference between baseline and subsequent child-based quality measures (e.g. range of movement) will be able to be detected with >90% power (where baseline percentage is around 50%; power will be greater where the baseline percentage is smaller or larger than 50%).

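### The stated time points for the child musculoskeletal model leave out baseline, although the child power statement is for a difference from baseline

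*Protocol article*

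**What the plan says.** Under Outcome measures, the paragraph on longitudinal outcomes of the children states: "Specific musculoskeletal measurements will be modelled from data collected at 6, 12 and 24 months".

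Four other statements in the protocol article bear on this:

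- **Assessment schedule (Outcome measures).** For the older group, "children aged 6–18 years will be assessed at baseline, 6, 12 and 24 months". For the younger group, "Children aged less than 6 years will be assessed at 6 monthly intervals"; baseline is not named there.
- **Child power statement (Estimated sample size and power of the study).** The effect is "A 10% arithmetic difference between baseline and subsequent child-based quality measures", which "will be able to be detected with >90% power". The example given is range of movement, and the baseline percentage is taken as about 50%. The expected number of children is 614, being 80% of 768 eligible.
- **Research design.** The study is described as before and after.
- **Statistical analyses.** Primary analyses are to assess change over time, including in the children's clinical outcomes.

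No section says that baseline enters the musculoskeletal model, either as an outcome or as a covariate.

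**The concern.** Range of movement is a musculoskeletal measurement, so the modelling sentence and the power statement concern the same kind of outcome. One uses three follow-up occasions; the other needs baseline and a follow-up. An analyst who followed the modelling sentence literally would fit a model with no parameter for the difference that the sample size was judged against.

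Any change between baseline and 6 months, the first period after the intervention is introduced, would then not appear in the child results. A flat course from 6 to 24 months could mean no change at all, or a change already complete by 6 months, and the model could not tell these apart.

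The omission also looks specific. In the same section the questionnaire, the knowledge quiz and the schedule for children aged 6 to 18 all name baseline before the same three follow-ups.

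**Working it through.** **Inputs from the article.** 614 children; baseline about 50%; difference 10 percentage points; power above 90%; model occasions 6, 12 and 24 months.

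**Assumptions, not in the article.** Two-sided 5% level; all 614 children measured at each occasion; no clustering; the shapes of change and within-child correlations shown below.

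**1. The plan's own figures.** 0.80 × 768 = 614.4, so 614 reproduces.

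Power with occasions treated as independent is Φ{[d√n − 1.96√(2p̄(1−p̄))] / √(p₁(1−p₁) + p₂(1−p₂))}, where p̄ is the mean of p₁ and p₂ and √614 = 24.779.

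For 50% against 60%: d√n = 2.478, √(2 × 0.55 × 0.45) = 0.7036, and √(0.25 + 0.24) = 0.700. Then (2.478 − 1.379)/0.700 = 1.570, which gives **94.2%**. This agrees with the stated power, so that claim rests on a contrast between baseline and a follow-up.

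The paired form is Φ{d√n/√V − 1.96}, with V = p₁q₁ + p₂q₂ − 2ρ√(p₁q₁p₂q₂) and q = 1 − p. At an assumed ρ of 0.3, V = 0.490 − 0.147 = 0.343 and power is 98.8%. At ρ of 0.5, V = 0.490 − 0.245 = 0.245 and power is 99.9%.

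**2. What remains without baseline.** The widest contrast left is 6 against 24 months. Suppose the percentage goes from 50% to 60% over 24 months.

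- *Linear change.* 6/24 of the 10 points, or 2.5, has occurred by 6 months. This leaves 52.5% against 60%, a difference of 7.5 points, with d√n = 1.858.
  - Independent: (1.858 − 1.96 × 0.7016)/0.6996 = 0.691, giving 75.5%.
  - Paired, ρ = 0.3: V = 0.4894 − 0.1468 = 0.3426; 1.858/0.5853 − 1.96 = 1.215, giving about 89%.
  - Paired, ρ = 0.5: V = 0.4894 − 0.2446 = 0.2447; 1.858/0.4947 − 1.96 = 1.797, giving about 96%.
- *Half the change by 6 months.* This leaves 55% against 60%, with d√n = 1.239.
  - Independent: (1.239 − 1.96 × 0.6991)/0.6982 = −0.188, giving 42.5%.
  - Paired: V = 0.3413 at ρ = 0.3 and 0.2438 at ρ = 0.5, giving about 56% and 71%.
- *All the change by 6 months.* Nothing remains to detect.

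| Contrast | Points | Independent | Paired, ρ 0.3 | Paired, ρ 0.5 |
|---|---|---|---|---|
| Baseline to follow-up | 10 | 94.2% | 98.8% | 99.9% |
| 6 to 24 months, linear | 7.5 | 75.5% | 89% | 96% |
| 6 to 24 months, half by month 6 | 5 | 42.5% | 56% | 71% |

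**3. Information on a linear slope.** The sum of squares of time about its mean is 110.25 + 20.25 + 2.25 + 182.25 = 315 for 0, 6, 12 and 24 months (mean 10.5). It is 64 + 4 + 100 = 168 for 6, 12 and 24 months (mean 14). So 168/315 = 53% is kept.

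**The case against.** The best defence is that the sentence does not say baseline is excluded. It may be a loose list of follow-up visits in an outcomes paragraph, with model detail left to the pre-specified statistical plans that the article promises. Read with the schedule and the power statement, the authors may well have intended to use baseline. That is plausible, and the sentence may be a drafting slip. It does not remove the point, because the article does not leave the time points open. It states them, and they disagree with its own power statement.

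Several stronger readings are tempting but not supported:

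- *That change from baseline cannot be estimated in this study.* This is true only of the model as written. Baseline is scheduled for ages 6 to 18, and for younger children too if their 6-monthly series starts at entry. Trends from 6 to 24 months also remain estimable, so the research question on time trends in adverse outcomes is weakened, not lost.
- *That the whole study is powered on this contrast.* It is the contrast of the child power statement only; the professionals' questionnaire has its own.
- *That power falls to 76%.* That figure needs a linear change and independent occasions. The article plans models for correlated data, and pairing recovers much of the loss.
- *That the children lose a clean pre-intervention measurement.* Research design defines baseline as preceding implementation for clinician measures, and the database holding the child data is itself part of the intervention. The article does not show how clean the child baseline is.
- *That leaving out 18-month visits is an error.* Only children under 6 would have them. Modelling the occasions common to all ages is a legitimate choice.
- *That the target is change from baseline to 24 months.* No section names it; the power statement refers only to later measures in general.

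**Conclusion.** The point holds as an internal contradiction. The modelling sentence lists follow-up occasions only, while the power statement, the assessment schedule and the before-and-after design all presuppose a baseline. Followed as written, the model lacks the contrast to which the stated power applies and cannot show change in the first 6 months.

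The stated power is not itself wrong. How much is lost cannot be fixed from the article: it ranges from modest (linear change, well-correlated paired data) to complete (all change by 6 months). All the figures above assume a two-sided 5% level, full attendance and no clustering, so they illustrate the loss and do not predict it.

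**What to change.** Reword the sentence along these lines: 'Musculoskeletal measurements will be analysed using the baseline assessment together with the 6-, 12- and 24-month assessments, with baseline as the reference occasion.' The analysis then contains the contrast in the power statement. The 18-month visits of children under 6 may be included as well, but this is not essential.

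The cost is one sentence. The scheduled assessments already provide for baseline, so no new data collection is needed. The Trial status section says that data collection continues to the end of 2015 and that nothing has yet been extracted from the clinical outcomes database. At that stage the change can still be made without sight of the child results.

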### Statistical analyses

Statistical plans addressing each specific research question will be pre-specified, to prevent bias due to post hoc analyses. Cross-sectional data will be examined and reported; however, primary analyses will focus on the longitudinal design of this study, assessing change over time in AHP evidence-based practice behaviours and in clinical outcomes for participating children.

Quantitative analyses will be carried out with multivariate statistical models such as population-averaged generalised estimating equations and subject-specific generalised linear and latent mixed models. These models allow for correlated longitudinal data structures and intraclass correlation coefficients (required due to children being clustered within AHPs and AHPs within organisations). In addition, these models can include outcomes of mixed types including counts, ordered and unordered responses, and dichotomous and metric outcomes. Potential confounders will be examined, and study sites will be treated as covariates to account for differing adoption of new practice rates. The significance of the covariates will be ascertained with 95% confidence intervals.

Qualitative focus group and interview data will be digitally recorded and transcribed, coded and analysed using a grounded theory approach to thematic analysis [39]. Themes within and between participants, and groups of participants, will be used to understand the feasibility and acceptability of the knowledge broker role and aligned evidence-based practices within the different organisations.

### Estimated sample size and power of the study

Based on organisational commitment to the project, and expected workforce changes during the course of the study, it is anticipated that 80% of the eligible AHPs will take part in the study (i.e. 192 participants from an estimated 240 eligible AHP participants across all partner organisations). Calculations indicate that this sample will be sufficient to detect a difference of 6 points on the Best Service Best Time Evaluation with >90% power.

Pre-study estimation of the number of participating children suggests a sample size of 614 may be achieved (80% of the 768 eligible children identified across all partner organisations).

A 10% arithmetic difference between baseline and subsequent child-based quality measures (e.g. range of movement) will be able to be detected with >90% power (where baseline percentage is around 50%; power will be greater where the baseline percentage is smaller or larger than 50%).

